## Abstract

**Background:**

Depressive and anxiety disorders are a very common, serious and underdetected problem in homes for the elderly. Elderly persons in residential homes are at high risk for developing major depressive and anxiety disorders, and, therefore, deserve attention with regard to prevention.

**Methods/Design:**

This protocol describes a randomised trial on the feasibility and (cost) effectiveness of a stepped-care programme for prevention of depressive and anxiety disorders in homes for the elderly. The main outcome measure is the incidence of depressive and anxiety disorder in one year with a two years follow up. Secondary outcomes are symptoms of depression and anxiety, quality of life, direct health care costs and satisfaction with treatment.

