### Data collection

#### Primary outcome

##### Depressive/anxiety disorder

Both the intervention and control participants will receive blinded independent assessment interviews of depression and anxiety status with the Mini-International Neuropsychiatric Interview (M.I.N.I.), at baseline, 3, 6, 9, 12 and 24 months (see Table 1). The M.I.N.I. is a short structured diagnostic interview for DSM-IV and ICD-10 psychiatric disorders. With an administration time of approximately 15 minutes, it was designed to meet the need for a short but accurate structured psychiatric interview for multicenter clinical trials and epidemiology studies and to be used in outcome tracking in non research clinical settings [32].

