### Sample size

Based on the prospective data of the Longitudinal Ageing Study Amsterdam (LASA) we conservatively estimate the incidence rate of depressive and/or anxiety disorder of elderly with symptoms of anxiety and/or depression within two years at 35% [33,52]. Our aim is to reduce incidence of full blown anxiety and depression disorders in the prevention group to 20%. To be able to detect this reduction (alpha = 0.5 and power = 0.80) 134 completers are needed, 67 in both conditions [53]. In the population of elderly persons in residential homes, substantial drop out (attrition) is expected because of illness and mortality. This is estimated at 20%, so therefore we need 172 participants. We know from previous projects that two thirds of subjects complete the CES-D, and we assume 40% will score 16 or more [22]. We estimate that 20% of these subjects already have a depressive and/or anxiety disorder and therefore will be excluded. With 80% consenting for randomization, we conservatively need to screen 1200 residents to find 86 residents per arm.

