### Analysis

To examine differences on the primary outcome, survival analysis will be used. The secondary outcome measures are analysed using random coefficient analyses. The analyses will be performed according to the "intention to treat" principle. Additionally, data will be analyzed according to the per protocol principle. Differences in total costs between both groups are assessed and confidence intervals are estimated using bias-corrected and accelerated bootstrapping with 2000 replications [54]. Cost-effectiveness and cost-utility ratios will be calculated by dividing the difference in total costs between the intervention and usual care group by the difference in the clinical effect measures and QALYs between the treatment groups. Uncertainty around the cost-effectiveness and cost-utility ratios will calculated using the bias-corrected percentile bootstrapping method (5000 replications) [55]. The bootstrapped cost-effect pairs were plotted on a cost-effectiveness plane.

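### The main outcome is declared at one year but the sample size is built on two-year rates, so the stated 80% power does not apply to it; 67 per arm falls short of 80% at either horizon

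*Protocol article*

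**What the plan says.** The abstract (Methods/Design paragraph) defines the main outcome: "The main outcome measure is the incidence of depressive and anxiety disorder in one year with a two years follow up".

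The Sample size section uses a different period. It puts "the incidence rate of depressive and/or anxiety disorder of elderly with symptoms of anxiety and/or depression within two years at 35" per cent, citing prospective cohort data. It continues: "Our aim is to reduce incidence of full blown anxiety and depression disorders in the prevention group to 20" per cent, with no separate period for that target. The operating characteristics are printed as "alpha = 0.5 and power = 0.80", and the result is "134 completers are needed, 67 in both conditions". After an allowance of 20% for attrition, the target is 172 participants, 86 per arm.

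Under Primary outcome, the MINI interview is scheduled "at baseline, 3, 6, 9, 12 and 24 months". The Analysis section says: "To examine differences on the primary outcome, survival analysis will be used".

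**The concern.** A power statement holds for one endpoint over one period. Here the declared outcome is one-year incidence, while the event rates behind the sample size are two-year rates. Fewer events will have occurred by 12 months than by 24, so the two-year figure cannot be carried over to a one-year comparison.

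Two things are at stake. Readers would take the declared one-year result to have 80% power when the article gives no basis for that. And because the diagnosis is made at both 12 and 24 months, the article leaves two results that could each be presented as the main one.

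**Working it through.** **Inputs from the Sample size section:** control rate 0.35 and intervention rate 0.20 (read as two-year rates), power 0.80, 67 completers per arm, 86 randomised per arm.

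**Assumptions of this check:** alpha is two-sided 0.05 (0.5 is printed and sidedness is not stated). One-year rates are not in the document and have to be assumed.

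**1. The plan's own figure, at two years.** With p̄ = 0.275 and difference 0.15:

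n per arm = [1.96·√(2·0.275·0.725) + 0.8416·√(0.35·0.65 + 0.20·0.80)]² / 0.15² = (1.2377 + 0.5239)² / 0.0225 = 137.9, so 138 per arm.

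| Variant for 35% vs 20%, 80% power | n per arm |
|---|---|
| Unpooled variance | 136 |
| Arcsine | 137 |
| Continuity-corrected | 151 |
| Log-rank (Schoenfeld): 73 events / 0.275 = 265 in total | about 133 |
| One-sided 0.05 | 109 |
| Alpha 0.5 as printed, two-sided | 41 |
| Alpha 0.5 as printed, one-sided | 13 |

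None gives 67 per arm. The printed total of 134 lies within 3% of the per-arm requirement of 138, so it looks as if a per-arm number was used as the total.

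**2. Power at two years with the stated numbers.**

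z = (0.15·√67 − 1.2377) / 0.6225 = −0.016, so power is 49.4% (log-rank 51.5%). With all 86 per arm contributing it is 59.7%.

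**3. Power at one year, constant hazard.** The one-year rates become 1 − √0.65 = 19.4% and 1 − √0.80 = 10.6%.

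Expected events among completers fall from 67 × 0.55 = 36.9 to 67 × (0.194 + 0.106) = 20.1.

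z = (0.0882·√67 − 0.9889) / 0.5007 = −0.533, so power is 29.7% (log-rank 31.3%). At 86 per arm it is 36.6%. For 80% power, 256 completers per arm would be needed.

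**4. Other assumptions about year one.** The same share of each arm's two-year incidence is taken to fall in year one:

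| Share in year one | Rates | Power, 67 per arm | Power, 86 per arm |
|---|---|---|---|
| Half | 17.5% vs 10% | 24% | 30% |
| 60% | 21% vs 12% | 29% | 36% |
| Three quarters | 26.25% vs 15% | 36% | 45% |
| 80% | 28% vs 16% | 39% | 48% |
| All | 35% vs 20% | 49% | 60% |

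A further case: if the arms separate only after the three months of watchful waiting, and the two-year rates are kept, the one-year rates are 19.4% and 11.9%. Power is then 22% at 67 per arm and 27% at 86.

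**5. Separating the two causes (constant hazard).**

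| Completers per arm | Two years | One year |
|---|---|---|
| 134 | 78.8% | 52.6% |
| 67 | 49.4% | 29.7% |

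Reading down the two-year column, the numbers cost about 29 points. Reading across, the horizon costs about 20 points at 67 per arm and about 26 at 134.

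**The case against.** The one-year phrase appears once, in an abstract, in a sentence that also mentions two years. The body is compatible with a two-year horizon: a two-year planning rate, MINI interviews to month 24 under the primary-outcome heading, and a survival analysis that can use all of them. It may be the abstract that is loosely worded. This is fair, and it bears on which place to correct. It does not remove the mismatch. If one year is meant, the sample size belongs to another endpoint; if two years is meant, the abstract is wrong.

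The 30% is not a figure of the document. It depends on a constant hazard and on 67 per arm being observed at one year. The article does not say when the 20% attrition accrues, and a survival analysis also uses partial follow-up, so the effective number may lie between 67 and 86 per arm. This stands, and is why ranges are given. Every case tried remains well below 80%.

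A reader might infer that the horizon mismatch alone takes power from 80% to 30%. The document's figures do not support that: the stated number does not deliver 80% at two years either, and the horizon accounts only for the step from about 49% to about 30%. A reader might also infer that declaring 24 months primary restores the stated power. It does not.

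The Analysis section's silence on the horizon, and on the type of survival model, is detail commonly left to a full protocol or analysis plan. It is not counted as an error here.

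**Conclusion.** The point stands as an inconsistency in the document. The outcome declared in the abstract and the period behind the sample size differ, nothing in the article reconciles them, and the stated 80% power does not apply to the declared outcome.

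On size, two statements should be kept apart. At the stated 67 completers per arm, the two-year comparison has about 49% power; this needs only the planning rates and alpha read as two-sided 0.05. The one-year comparison has about 30% under constant hazard, and about 24% to 49% across year-one shares from half to all.

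The mismatch is material by itself: with 134 per arm, one-year power would still be about 53% against 79% at two years. That 134 was a per-arm figure is an inference from how closely it matches, not something the article says.

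**What to change.** Name one primary horizon and use it in both the abstract and the Sample size section. Two routes are open:

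- **24 months.** Define the primary outcome as time to first MINI depressive or anxiety disorder through 24 months, with one-year incidence as a named secondary outcome. Restate the power at the planned number as about 49%, or about 60% if all 86 per arm contribute. Changing the wording without restating the power would leave the 80% claim uncorrected.
- **One year.** Keep the abstract's outcome, replace 35% and 20% with justified one-year rates, and restate the power (about 30% under constant hazard).

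In either case correct the printed alpha, state its sidedness, and say whether 134 is a total or a per-arm figure.

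No new assessment is needed, since the 24-month MINI is already scheduled. The cost is a less favourable power statement. If 80% is to be kept at two years, the requirement is 2 × 138 = 276 completers, or 276 / 0.8 = 345 randomised, against the planned 172. The 24-month route also has a measurement limit: the second year has a single assessment, so the timing of onset there is coarse.

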**Discussion:**

The number of studies examining the effects of preventive interventions on the incidence of mental disorders in the elderly population is very small. However, indicated prevention by means of a stepped-care programme seems to be an important option for decreasing the burden of illness for residents and their caregivers. This study contributes to the body of knowledge in this field. Positive effects may contribute to further use and development of tailored, (cost-) effective and easy to use interventions in a preventive stepped-care programme.

**Trial Registration:**

The Dutch Cochrane Centre, ISRCTN27540731

## Background

In homes for the elderly, depressive and anxiety disorders are very common and have a large impact on the well-being and daily functioning of the residents. In 2002 over 90,000 of the nearly one million elderly persons in the Netherlands, aged 75 years or older, lived in a residential home [1]. Up to 30 percent of these residents develop symptoms of depression and anxiety, such as apathy and feelings of loneliness and hopelessness [2]. In about 30 to 35 percent of residents with symptoms of depression and anxiety, these symptoms eventually develop into major depression and generalised anxiety disorder [3,4]. These disorders are often associated with a poor prognosis and with excess mortality, disability, handicap and service utilisation. [5-11]. Treatment can reduce the illness burden in the population, but only to a moderate extent [12]. Therefore, prevention may be an attractive option.

Indicated prevention, as opposed to universal prevention (aimed at the general population regardless of risk status) or selective prevention (aimed at high-risk groups), aims to counter the onset or development of a disorder in those who already have symptoms. Indicated prevention may be a successful approach since it targets high-risk persons who are identified as having minimal symptoms foreshadowing mental disorders. Risk factors for depression and anxiety disorders in the general population are known; a large naturalistic follow-up study among persons 55 years of age in the community showed that a set of six indicators explained 83% of the total prognostic variance. The prediction model include symptoms of depression and/or anxiety disorder, functional limitations, small network, female gender, low education or suffering from chronic diseases [13]. These characteristics are very common among residents of homes for the elderly, which makes this a population at high risk for depressive and anxiety disorders. Indicated prevention studies, in different target populations, have shown that several interventions are capable of reducing the incidence of depression and anxiety disorder up to approximately 30% [14]. From an ethical and societal point of view, indicated prevention is preferred to universal prevention and selective prevention. Prevention activities may increase fear or uneasiness in the target population; however, this is legitimated most for people who already suffer of symptoms and are known to have a high risk.

Although caregivers in the homes recognize the impact of the problem as described earlier, symptoms of depression and anxiety are rarely identified and labelled as such [15,16]. A substantial part of residents of homes for the elderly suffers from physical co-morbidity. Symptoms of depression and anxiety disorder like apathy and weariness may also be ascribed to physical illnesses [17]. This makes that symptoms of anxiety and depression are often interpreted only as consequences of decline rather than problems that require intervention. Physical illness in the elderly is most of the time progressive and hard to cure. Depressive and anxiety disorders, however, have more optimistic possibilities for prevention and treatment [14,18,19]. Moreover, as the population is ageing rapidly and the policy in the Netherlands is to facilitate independent living as much as possible, the level of psychological and physical frailty in homes for the elderly has been increasing rapidly. At the same time, medical care is also changing: General Practitioners (GPs), who are responsible for medical care in the residential homes in the Netherlands, have for instance halved the number of house visits since 1987 [20]. In addition, most homes suffer from staff deficits, in which cases the quality of care is threatened [21]. Therefore, efficient use of the available, scarce resources, as supplied by this stepped care protocol, is of great importance.

This study focuses on the feasibility and (cost-) effectiveness of a stepped-care intervention to prevent the onset of full-blown depressive and anxiety disorders among residents of homes for the elderly with subthreshold anxiety and/or depressive symptoms. The stepped-care protocol chosen in this study is at the moment already being used in a related study for vulnerable elderly persons in the community [22]. This program is based on the assumption that stepping up from lower, less intensive to higher, more intensive levels of preventive activities, based on monitoring outcomes, may increase the (cost) effectiveness of the programme and maximize efficiency of resource allocation [23-25]. Moreover, it is reasonable to assume that different people prefer and require different levels of preventive activities. Some may be helped with working through a self-help manual, others could benefit from a minimal-contact psychotherapy, and still others may require a form of pharmacotherapy or more intensive individual psychological treatment. In this study we focus on residents with subsyndromal symptoms of depression and/or anxiety who do not meet the criteria of a full-blown disorder. A stepped-care protocol may be particularly relevant for this group. Residents that already suffer from disorders might be better managed through more complex and intensive collaborative-care models [24,26]. The primary aim of the present trial is to investigate whether a stepped-care protocol based on monitoring and evidence-based interventions is able to prevent the onset of depressive and anxiety disorders in residents of homes for the elderly as compared to care as usual. Secondary aims include reducing the level of symptoms of depression and anxiety, improving quality of life, reducing costs of health care consumption and improving satisfaction with treatment. The feasibility of this protocol is judged on the basis of motivation and evaluation of residents, caring staff and general practitioners. Organisational barriers are also assessed.

## Methods/Design

### Design

To evaluate the effects of the stepped care protocol, a randomised, controlled trial in residential homes for the elderly will be carried out. Homes for the elderly in Amsterdam will be selected. Caring staff and GPs of the participating residents will be involved in the intervention protocol. Participants are asked to give informed consent referring to the stepped care interventions, the randomisation and informing their GP during the intervention programme. The medical Ethics Committee of the VU medical centre in Amsterdam approved the study design.

### Participants

Participants will be recruited among residents of homes for the elderly by means of a screening procedure using the Centre of Epidemiologic Studies Depression scale (CES-D 20) as a screening instrument [27-29]. Residents with a score of 16 and more are invited for a follow-up diagnostic interview. This score is widely accepted as an indication for symptoms of depression and/or anxiety [30]. Residents meeting criteria for major depression and/or clinical anxiety disorder according to the Mini International Neuropsychiatric Interview (MINI) [31,32] or suffering cognitive impairment according to the Mini Mental State Examination (MMSE <21) are excluded. Residents capable of informed consent and with sufficient understanding of the Dutch language, are eligible for the study.

### Interventions

#### Stepped-care protocol

Our intervention protocol is based on the protocol of The Prevention of Anxiety and Depression in Late Life consortium (PADLL, in which several Dutch universities and the national mental health institute collaborate) [22]. This consortium designed a generic stepped-care intervention protocol to be tested across different health care settings, different groups of elderly persons and different forms of prevention (prevention of episodes vs. relapse prevention). For use in homes for the elderly, we selected the interventions that seemed to be most suitable for this frail and isolated population. In organizing this stepped-care approach, evidence-based guidelines are used as far as possible. Staff in the homes for the elderly and mental health nurses will be contracted to cooperate in the stepped-care protocol. One caregiver will coordinate the care. Necessary training will be provided. When residents show continuously elevated CES-D scores, GPs of the residents will be involved.

The protocol contains the following steps (see Figure 1):

##### Step 1: watchful waiting

The first step of the program consists of watchful waiting, since frequently (up to 50% of the cases) the complaints disappear without active intervention [33]. Residents will be included in the intervention group in step 2 after a three months period of persisting symptoms.

##### Step 2: biblio-therapy and a signal to the GP

Participants, who still have symptoms of depression and anxiety after 3 months of watchful waiting, as measured with the CES-D, are informed about the possibility of learning to cope with these symptoms by a self-help course for coping with depression and anxiety with an accent on activity scheduling. Self administered treatments for depression and anxiety have proven to be successful in clinical practice and for older adults [19,34-39]. Staff will be trained to accompany and stimulate the residents while working through the course in their own tempo. At the same time, GPs will be involved by informing them about the persisting symptoms. After a period of three months the third measurement will take place.

##### Step 3: Life review intervention and consult GP

When symptoms persist, residents are informed that they qualify for a more specific treatment: the life review with problem solving accents. Life review is a promising treatment for elderly with symptoms of depression [40]. The effect for elderly with symptoms of anxiety is not explicitly studied, however support exists for a decrease in disempowerment themes, such as anxiety and despair [41]. The intervention will be delivered by a mental health nurse trained and supervised in the intervention. This training will be given by experienced supervisors of the national mental health institute (Trimbos institute), who adapted this intervention for the use in homes for the elderly in the Netherlands. GP's of participants in step 3 receive advise to check for possible somatic causes of depression and anxiety symptoms (thyroid disease, vitamin deficiencies, Parkinson disease) or intake of depressogene substances (medication, alcohol). After a period of three months the fourth measurement will take place.

##### Step 4: consultation mental health specialist

In case the residents still have CES-D scores > 15, they will receive advice to consult their GP to consider medication (antidepressants) and/or consultation by a mental health specialist.

#### Usual care

In the Netherlands, residential homes provide daily care to the infirm elderly with significant limitations to daily living; if needed, they also provide basic medical care. Nurses and care workers supply generic care, while GPs are medically responsible. Residents assigned to the control group receive care as usual by staff of the homes and their GPs. Residents are informed that every three months measurements with CES-D and additional interviews take place in order to keep track of the symptoms.

### Data collection

#### Primary outcome

##### Depressive/anxiety disorder

Both the intervention and control participants will receive blinded independent assessment interviews of depression and anxiety status with the Mini-International Neuropsychiatric Interview (M.I.N.I.), at baseline, 3, 6, 9, 12 and 24 months (see Table 1). The M.I.N.I. is a short structured diagnostic interview for DSM-IV and ICD-10 psychiatric disorders. With an administration time of approximately 15 minutes, it was designed to meet the need for a short but accurate structured psychiatric interview for multicenter clinical trials and epidemiology studies and to be used in outcome tracking in non research clinical settings [32].

